**Figure 1 F1:**
[figure not shown]
Trial Process.

All outcome data are administered over the telephone and entered into a Microsoft Access database with built-in logic and range checks to allow for immediate correction of errors and insertion of missing data.

#### Ethical approving body

This research protocol has been granted full ethical approval by the University of Toronto Health Sciences Research Ethics Board.

### Recruitment rate

The participant recruitment rate for this trial is founded on three factors: (1) the ability of public health nurses and other health professionals to identify and refer mothers with depressive symptomatology (EPDS > 12), (2) the number of referred mothers diagnosed with major depression (based on SCID interview), and (3) participant acceptance of the trial. Based on the health regions’ birth rates, the assumption that approximately 13 % of mothers will experience PPD [15], and that less than 50 % of mothers seek treatment for PPD [44], we conservatively estimate that 20 % of depressed mothers will be detected by public health nurses and other health professionals each year. In one IPT trial that initially identified mothers with a self-report measure (for example EPDS > 12) before applying a clinical diagnosis (for example SCID), only 65 % of women with depressive symptomatology were diagnosed with major depression [78]. In another IPT trial, 64 % of patients identified with depressive symptomatology (for example CES-D) were diagnosed with major depression [139]. Research has demonstrated high maternal acceptance to completing the EPDS [130] and both of [name]’ breastfeeding [103] and PPD prevention trials [110,130] had good acceptance rates (> 66 %) to postpartum telephone-based interventions. Furthermore, in a review of maternal treatment preferences completed by [name], depressed mothers clearly indicated that they preferred ‘talking therapies’ [44]. For PPD IPT trials that were either clinic or group-based, acceptance rates of eligible mothers ranged from 51 % [77] to 68 % [79]. As such, we expect to recruit our sample size of 240 mothers with major depression in 2.5 years based on: (1) a public health department 20 % identification rate of mothers with EPDS scores > 12, (2) a conservative 50 % clinical diagnosis of major depression rate, (3) a 50 % maternal acceptance rate, and (4) a 15 % exclusion rate due to maternal use of antidepressants.

### Operational details

#### Telephone-IPT intervention

Mothers allocated to the treatment group receive 12 weekly IPT sessions, each session 50 to 60 min in duration and delivered over the telephone by a trained IPT nurse who receives weekly supervision by an IPT trainer ([name]). Within 72 h, the IPT nurse will either administer session 1 (if possible) or at least make an initial call to the participant to schedule session 1 (to occur within the week following enrolment). The scheduling of IPT sessions are based on mutual availability between the mother and IPT nurse. IPT is administered according to the standardized manual by Stuart and Robertson [56,140], with some modifications to accommodate the postpartum context of depression. These modifications are based on previous IPT trials for PPD [141].

As conducted in standard IPT clinical practice, a minority of trial participants identified as either in acute crisis at the end of treatment, or who are progressing however remain significantly symptomatic, thus would benefit from extending the course, may be offered up to four additional IPT sessions (that is, conduct 12 or a maximum of 16 sessions per trial participant, as appropriate). A full course of therapy must be completed within 16 weeks to account for any additional sessions and/or occasional scheduling conflicts or difficulties.

The initial sessions (1 to 3) will be concerned with placing the depression in an interpersonal context, reviewing the mother’s current and past interpersonal relationships, and relating problematic aspects of their relationships to the mother’s current depression. The IPT nurse and mother will collaboratively identify the problem area(s) most related to the episode and set treatment goals. During the intermediate sessions (4 to 9), the nurse will focus on the interpersonal difficulties identified by the mother, and utilize the IPT therapeutic guidelines to work through these focal problems. Based on previous IPT trials [77,141], common postpartum IPT problem areas include conflict with partner or extended family (interpersonal disputes), loss of social/work relationships (role transition), and losses unassociated with the birth, such as the death of a significant other (grief). In the final sessions (10 to 12), the nurse will reinforce the mother’s progress and efforts, her sense of competence in overcoming depression, consolidate her gains, discuss feelings or worries about concluding therapy, and work with the mother to develop plans should the depression recur. All sessions are audio-taped for supervision and monitoring purposes.

#### IPT training

Recruited nurses undergo extensive IPT training as lead by highly skilled and experienced IPT supervisors, [name] and [name] (also psychiatrist co-investigators) comprised didactic learning and supervised clinical practice. Previous studies have demonstrated that nurses can be effectively trained to provide IPT [68-70]. Prior to trial initiation, IPT nurses read and become familiar with the Interpersonal Psychotherapy manual (by Stuart and Robertson) and the postpartum modifications based on previous PPD IPT trials [141]. Each IPT nurse attends a didactic workshop with videotape presentations (minimum 5 h duration), meeting the standard for training of IPT therapists.

In addition to attending a workshop and reading about IPT, study nurses must successfully complete two supervised IPT clinical cases of 12 sessions each with patient volunteers who have been diagnosed by referring psychiatrists with PPD. The first case is done in person, and the second case is conducted by telephone following one initial face-to-face meeting with the nurse. All sessions are audio-recorded and reviewed in full by the supervisors who provide weekly supervision and feedback on the clinically applied principles and therapeutic techniques of IPT. An IPT nurse is considered ‘fully trained’ and prepared to administer the intervention to enrolled trial participants when she demonstrates a high degree of therapeutic competence and adherence (as monitored by IPT supervisors) and successfully completes IPT administration to the two test cases.

#### IPT supervision

While some researchers suggest that IPT therapists who perform well on their first supervised case do not require further intensive supervision [142], to ensure ongoing treatment fidelity, all fully trained and trainee IPT nurses are required to participate in weekly group supervision meetings. IPT nurses are also able to contact intervention supervisors as necessary to address immediate concerns.

#### IPT rating

Audio-recorded IPT sessions are randomly reviewed by an independent and IPT-trained rater to document treatment fidelity using the IPT Adherence Checklist. Adherence raters are trained to achieve > 90 % agreement with one of the IPT expert trainers.

#### Compliance

It is expected that 80 % of the intervention group will receive IPT due to the specific inclusion/exclusion criteria, informed consent procedures, and intervention compliance procedures. Some of the participants will drop out because of their preference for in-person therapy, scheduling difficulties, unsuccessful contact post-randomization or due to crises that can in some cases require contact with child protection service agencies, public health and/or their family physicians. In this trial, treatment compliance means the completion of at least 10 IPT sessions. Monitoring compliance of the intervention are three-fold: (1) IPT nurses’ completion of IPT Activity Logs for each participant, (2) supervision of the IPT intervention as provided by [name] and [name], and (3) mothers’ evaluations of their IPT experiences.

#### Loss to follow-up

Maternal questionnaires were designed to require low levels of literacy and relatively little time to complete; they have been used previously with postpartum mothers and examined for clarity, comprehension, and ease of use. In particular, all measures (except the DAS and ECR-R) were used as outcome measures in [name]’ PPD prevention trial with no difficulty. Attrition is a significant threat to both internal and external validity in intervention and longitudinal studies, as the average retention rate of 6-month to 2-year follow-up studies has been estimated at 62 % [143]. The following proactive telephone strategies [144] are employed to encourage high retention rates. Each questionnaire contains a contact form for the IPT nurse to record the date, time of call, status of call (for example busy, call back, no answer, and so on), and comments. Participants are telephoned during their stated’best time to contact’ period, surveys are cycled up to three times per day, and if possible, messages are left. Directory assistance is telephoned for all disconnected and wrong numbers. The desired goal is a minimum response rate of 90 %. Additional strategies to ensure a low attrition rate, based on a Cochrane review [145] and other research [146], are as follows: (1) obtaining a secondary contact number (such as the participant’s mother) from each participant at recruitment, (2) conducting telephone reminder calls of impending interviews, and (3) providing a small token of appreciation provided to all mothers who complete the 36-week post-randomization interview. Similar strategies were used in [name]’ PPD prevention trial [110] with good results (retention rate = 87 % at 12 week assessment and 85 % at 24 week assessment).

### Statistical analysis plan

#### Primary analysis

Data will be analyzed using SAS software and an intent-to-treat approach will be used. Every effort will be made to collect follow-up data from all participants. We will not impute a score for missing primary outcome data. A two-sided significance level of 0.05 will be used for the primary outcome; a significance level of 0.01 (two-sided) will be used for secondary and other outcomes to account for multiple comparisons. The demographic and other baseline variables will be compared between study groups using descriptive statistics (means, standard deviations, proportions). For the primary analysis, a two sample two-sided test of proportions will be used to compare the difference in the incidence of PPD (major depression using the SCID) at 12 weeks post-randomization between the intervention and control groups. For secondary analyses, the statistical method to compare groups will depend on the distribution of the outcome variable in question. For binary variables (for example EPDS score > 12), a contingency table chi-square for a 2 × 2 table will be calculated and presented together with estimates for the relative risk, relative risk reduction, absolute risk reduction, and the number needed to treat. The corresponding 95 % confidence intervals for each estimated parameter will also be provided. Covariate variable adjustment will be achieved using logistic regression. For ordered categorical variables, a chi-square for trend will be calculated. Relative risks for each category versus a base category will be presented. Continuous variables with repeated measurement (such as anxiety) will be first analyzed using a single, repeated measures MANOVA consisting of group and time factors to test for the study’s overall intervention, time, or interaction effect. Following the detection of a significant effect, separate repeated measures 2-factor analyses of variance (RANOVA) with appropriate contrasts will show the nature of the effect within each outcome variable. Covariate variable adjustment will be achieved using analysis of covariance and linear regression. Finally, the relationship between the number of IPT sessions on PPD, and other study outcomes will be assessed to determine an effective dose response.

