### Randomization procedure

Randomization is centrally controlled using a web-based randomization service, with stratification based on self-reported history of depression and province. This randomization service was successfully used by [name] in the PPD prevention trial [110]. Provincial stratification is planned, because postpartum care is based on practice standards set by a province’s Ministry of Health. As such, ‘standard postpartum care’ will be very different for each province.

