Given that (1) all the preceding studies used self-report measure to assess recovery (for example, no depressive symptomatology using a specific cutoff score) instead of a diagnostic interview such as the SCID, and (2) the proposed trial’s sample will be heterogeneous and include rural and urban mothers from diverse provinces, for the purpose of calculating the sample size, we have made the conservative assumption that 30 % of mothers in the control group will spontaneously recover and will not have major depression at the 12 week post-randomization assessment (70 % will remain clinically depressed) (Table 2). The sample size is based on the ability to detect a moderate decrease of 20 percentage points to a rate of 50 % among mothers in the intervention group. Our partners in the participating public health departments agree that a 20 % absolute decrease in the number of mothers with depression post-treatment is the minimum effect that would be considered clinically meaningful, warranting the time and effort to develop and implement an IPT program. A two-tailed α error of 0.05 was chosen, as there is insufficient empirical evidence of either risk or benefit associated with the proposed telephone-based IPT intervention. Thus, with 80 % power, a two-tailed α error of 0.05, and using a test of two independent proportions to find a 20 % reduction in the number of mothers with depression at 12 weeks post-randomization (immediately post-treatment for mothers in the intervention group), a sample size of 188 (94 per group) is required; we plan to enroll 240 to allow for up to 20 % loss to follow-up. This sample size also provides power to detect a 20 % absolute reduction in other secondary outcomes, such as anxiety.

**Table 2 T2:** Sample size differences between groups

**Control group depression rate**	**IPT group depression rate**	**Size per group**
75	55	88
70	50	94
5	45	96

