#### Public health

Currently, 24 public health departments across Canada (Ontario, Manitoba, Saskatchewan, and British Columbia) are assisting with recruitment for this trial. In Canada, public health departments receive notification of women who have given birth in their health region. As part of standard practice, each mother receives a telephone call or home visit from a public health nurse within the first few weeks postpartum following hospital discharge. During these interactions, public health nurses often administer the EPDS to assess maternal mood. A brief description is provided to mothers who are identified as experiencing depressive symptomatology (EPDS > 12) after the first 2 weeks postpartum (in order to avoid false-positives that are ‘maternity blues’). If verbal consent is obtained, the potentially eligible mother’s contact information is sent to the trial coordinator.

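### Randomisation is stratified by depression history and province, but the primary test ignores both; if the strata predict 12-week depression, the test is conservative and some available precision is given up

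*Protocol article*

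**What the plan says.** The Randomization procedure section of the protocol article describes central web-based allocation "with stratification based on self-reported history of depression and province"; the Self-referrals section repeats this. A reason is given for province only: standard postpartum care, which is the control condition, "will be very different for each province". No reason is given for history, and no section gives depression rates by province or by history.

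Under Statistical analysis plan, Primary analysis, "a two sample two-sided test of proportions will be used to compare the difference in the incidence of PPD" at 12 weeks, and "A two-sided significance level of 0.05 will be used for the primary outcome". The Justification for sample size section uses the same kind of test: "Thus, with 80 % power, a two-tailed α error of 0.05, and using a test of two independent proportions".

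The Primary analysis section also contains the sentence "Covariate variable adjustment will be achieved using logistic regression". It comes after the text has turned to secondary analyses and, within those, to binary variables. It names no covariates and is not linked to the primary test.

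**The concern.** Stratified randomisation makes the arms alike on the strata. If the strata predict the outcome, the difference between arms varies less from one hypothetical repetition of the trial to the next than it would under simple randomisation. A test that ignores the strata uses the larger, simple-randomisation variance. Its standard error is then too large, its confidence interval too wide, and its rejection rate under the null below the nominal 5%.

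Precision on the primary outcome is at stake, not validity. The design pays for the balance and the analysis does not collect the return. The separate-SAP argument does not remove the point, because the article names the primary test itself and sizes the trial on it.

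**Working it through.** **1. Reproduce the sample size.** Inputs from Justification for sample size: control rate 0.70 ("70 % will remain clinically depressed"), intervention rate 0.50, two-sided α 0.05, power 80%. With the pooled variance and no continuity correction:

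n = [1.960 × √(2 × 0.60 × 0.40) + 0.842 × √(0.70 × 0.30 + 0.50 × 0.50)]² / 0.20² = (1.358 + 0.571)² / 0.04 ≈ 93 per group.

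The article states 94, and power at 94 per group is 80.4%. Allowing for 20% loss, 188 / 0.8 = 235, and 240 × 0.8 = 192 evaluable. The plan's figures hold for the unadjusted test.

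**2. Assumptions for the check.** The article gives no rates by stratum, so these are assumed: history split 50:50; four provinces (the number named in the Public health section) at 55/15/15/15%; a history difference h of 0 to 30 percentage points; a province spread s of 0 to 20 points, with one of the 15% provinces s/2 above the average and another s/2 below; the same 20-point effect in every stratum; 94 women per arm, balanced exactly within the eight strata (26 or 7 per arm in each).

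**3. Standard error.** The variance the unadjusted test uses is (0.21 + 0.25)/94 = 0.46/94, giving a standard error of 0.0700. The variance under balanced strata is (0.46 − 2V)/94, where V is the between-stratum variance of the rates: V = h²/4 + (28/94)(s/2)².

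- h = 0.20, s = 0: V = 0.0100; √(0.46/0.44) = 1.022, so 2.2% too large.
- h = 0.30, s = 0.20: V = 0.0225 + 0.0030 = 0.0255; √(0.46/0.409) = 1.060, so 6.0% too large.

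Under the null (both rates 0.70) 0.42 replaces 0.46, and the second case becomes √(0.42/0.369) = 1.067. The expected type I error is then twice the upper normal tail beyond 1.96 × 1.067 = 2.09, or about 0.037.

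**4. Simulation.** 40,000 runs per scenario, pooled unadjusted z-test against a Cochran-Mantel-Haenszel (CMH) test over the eight strata. Monte Carlo standard error is about 0.2 points for power (√(0.8 × 0.2/40,000)) and 0.001 for type I error (√(0.05 × 0.95/40,000)).

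| History difference (points) | Province spread (points) | SE excess at planned effect | Power, unadjusted % | Power, CMH % | Gain (points) | Type I, unadjusted | Type I, CMH |
|---|---|---|---|---|---|---|---|
| 0 | 0 | 0.0% | 80.10 | 80.12 | 0.02 | 0.051 | 0.051 |
| 10 | 0 | 0.5% | 80.44 | 80.91 | 0.47 | 0.049 | 0.050 |
| 10 | 10 | 0.7% | 79.88 | 80.41 | 0.53 | 0.048 | 0.050 |
| 20 | 0 | 2.2% | 80.55 | 82.22 | 1.67 | 0.046 | 0.051 |
| 20 | 10 | 2.4% | 80.50 | 82.48 | 1.98 | 0.043 | 0.048 |
| 20 | 20 | 3.0% | 80.78 | 82.84 | 2.06 | 0.043 | 0.050 |
| 30 | 10 | 5.5% | 81.58 | 84.83 | 3.25 | 0.038 | 0.051 |
| 30 | 20 | 6.0% | 81.05 | 84.71 | 3.66 | 0.037 | 0.051 |

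Unadjusted power stays at about 80% or slightly above in every row. The CMH test keeps its nominal level even with only 7 women per arm in the small strata.

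**The case against.** The best defence is that design and analysis agree. The trial was sized on an unadjusted test and will be analysed with one; that test is simple, transparent and never exceeds its nominal error rate by more than simulation noise. This stands, and it limits the point to one of efficiency.

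A reader might infer more, in four ways that the documents do not support:

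- **That the trial falls short of its planned power.** It does not: the stated 94 per group reproduces for the unadjusted test.
- **That the standard error is too large whatever the data.** It is so only if the strata are prognostic. Different standard care by province makes that plausible but does not show that SCID recovery differs. The Consent section expects very few mothers to receive psychotherapy, and the exclusion criteria remove women on antidepressants or in individual psychotherapy at entry. For history, the article gives no rationale at all.
- **That the loss is much larger.** If 20% of outcome variance were explained, power would be about 88% and the unadjusted type I error about 2.8%. For history alone to explain that much, at 70% persistence with an even split, the two groups would have to differ by 2 × √(0.20 × 0.21) = 0.41, roughly 90% against 50%. Nothing in the article supports this. Reaching 88% by adding baseline EPDS also answers a different question, since EPDS is not a stratification factor.
- **That the logistic-regression sentence already covers the primary outcome.** Its position ties it to secondary binary outcomes, and it would yield an odds ratio, whereas the trial is sized on a risk difference. It does show that adjusted binary analyses are foreseen, so the change is in keeping with the plan.

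It is also fair that province strata may be sparse, because the Other health professionals section allows referrals from across Canada, and pooling adds a choice that must be fixed in advance.

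**Conclusion.** The mismatch between a stratified design and an unstratified primary test is in the text and is worth correcting, as an efficiency improvement rather than an error of validity. Over the assumed range, the cost is about 0 to 4 points of power, a standard error up to 6% too large at the planned effect (just under 7% under the null), and a type I error of about 0.037 to 0.05. A 20-point difference by history alone costs under 2 points of power.

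These sizes rest on assumed stratum rates and proportions, a constant 20-point effect, and near-exact balance of the evaluable women within strata; imperfect balance would change them. The direction does not depend on the particular values: prognostic, balanced strata make the unadjusted test conservative, and non-prognostic strata make no difference.

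**What to change.** Replace the primary test by one of the following:

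- a Cochran-Mantel-Haenszel test over the randomisation strata, reported with a Mantel-Haenszel risk difference and 95% confidence interval; or
- logistic regression of 12-week SCID status on arm, history and province, standardised over the sample to a risk difference with 95% confidence interval. Baseline EPDS, already collected (Table 1), may be added here as a prespecified covariate.

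State a rule for pooling sparse provinces, set blind to arm and outcome. Keep the unadjusted test as a supportive analysis and leave N at 240.

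The cost is a paragraph of text and a slightly more complex analysis, with no new data or participants. The Trial status section reports 212 women enrolled with recruitment still open, so the change and the pooling rule should be fixed and dated before any outcome is compared by arm.

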#### Consent

Two copies of the study explanation and participant consent form are mailed to each participant. A postage-paid, addressed envelope is included in the mailed package so that one copy of the signed consent form is returned to the trial coordinator and the other copy is retained by the participant for her own records. These informed consent procedures have been used effectively by [name] in previous trials [110,130].

With detailed informed consent procedures, it is expected that mothers will accept their group allocation following randomization. While most health professionals caring for participants and research nurses will be blinded, mothers cannot be. However, a formal telephone-based IPT PPD program does not already exist in the participating health regions, thereby ensuring no mother in the control group will receive the intervention. There will be no interference with usual medical/nursing care, which for some mothers may include antidepressant medication and/or psychotherapy. Very few mothers will have available and receive psychotherapy. As such, the actual number of trial participants in the control group who will receive psychotherapy will be very small; data about the presence of psychotherapy external to the trial will be collected during the health service utilization assessment. Information about interventions to treat PPD will be obtained from the participants and considered in the data analyses.

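### The planned session-count analysis cannot identify an effective dose: sessions are not randomised, extra ones follow poor response, and some fall after the 12-week outcome

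*Protocol article*

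**What the plan says.** The last sentence of the Primary analysis section says that "the relationship between the number of IPT sessions on PPD, and other study outcomes will be assessed to determine an effective dose response". It names no model, population or adjustment, and it attaches no caution to the stated aim.

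Other sections determine how a session count arises:

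- **Telephone-IPT intervention, top of the range.** The standard course is 12 weekly sessions. Extension is for "a minority of trial participants identified as either in acute crisis at the end of treatment" or for women "who are progressing however remain significantly symptomatic, thus would benefit from extending the course"; they "may be offered up to four additional IPT sessions".
- **Telephone-IPT intervention, window.** "A full course of therapy must be completed within 16 weeks", which leaves room for extension sessions and for scheduling problems.
- **Compliance.** The plan expects 80% of the intervention group to receive IPT. It attributes dropout to preference for in-person therapy, scheduling, failed contact and crises. It adds that "treatment compliance means the completion of at least 10 IPT sessions".
- **Main outcome measure.** The primary outcome is the SCID-I diagnosis at 12 weeks post-randomisation.

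**The concern.** An effective dose is a causal quantity: the number of sessions that produces a given benefit. The number a woman receives here is partly a consequence of how she is doing. At the top of the range, she gets more because she has not recovered or is in crisis. At the bottom, she gets fewer for reasons that may be related to prognosis. Randomisation balances the two arms, but it does not balance women with 8, 12 and 15 sessions.

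The 12-week outcomes have a second problem. Sessions may run to week 16, so a total count includes exposure that comes after the outcome it is meant to explain.

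At stake is a statement about how many sessions work. Followed as written, the analysis could suggest that extra sessions harm, that they help, or that they do nothing, when in truth the number makes no difference.

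**Working it through.** **Plan's own figures.** The dose-response analysis has none. The nearest is the primary sample size, 70% against 50% depressed with 80% power and two-sided 0.05:

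n per group = [1.96·√(2·0.60·0.40) + 0.8416·√(0.70·0.30 + 0.50·0.50)]² / 0.20² = (1.358 + 0.571)² / 0.04 ≈ 93.

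The plan states 94, which gives power 0.804. That figure reproduces, and this point does not touch it.

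**Time order.** With weekly sessions from the first week, session 12 falls at about week 12 and sessions 13 to 16 in weeks 13 to 16, after the primary SCID-I. A standard course delayed by scheduling can also run past week 12. All sessions end by week 16, so they precede the 24- and 36-week assessments. There the dependence on response remains but the timing fault does not.

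**Size of the bias when session number has no effect.**

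Inputs from the documents:
- 50% of the IPT arm depressed at 12 weeks (sample size justification);
- 80% receiving IPT, the 10-session threshold and up to four extra sessions.

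Assumptions not in the documents:
- the 80% have 10-12 sessions, evenly spread, and the other 20% have 0-9;
- a share *e* of still-depressed completers is extended to 13-16 sessions, and no recovered woman is;
- depression in low attenders, *q*, is 50-70%.

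Depression among completers is (0.50 − 0.20·*q*)/0.80, which is 50%, 47.5% or 45% for *q* = 50%, 60% or 70%.

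Example with *q* = 50% and *e* = 20%: the extended are 0.80 × 0.50 × 0.20 = 8% of the arm, all depressed by construction. Among completers not extended, depression is (0.50 − 0.10)/(1 − 0.10) = 44.4%. The gap is produced by the extension rule alone.

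A logistic regression of depression on session count, used only as one way to express the association, gives these odds ratios per session:

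| *e* | At least 10 sessions | Whole arm, *q* = 50% / 60% / 70% |
|---|---|---|
| 0% | 1.00 | 1.000 / 0.941 / 0.882 |
| 10% | 1.34-1.35 | 1.028 / 0.974 / 0.920 |
| 20% | 1.55-1.57 | 1.053 / 1.000 / 0.951 |
| 30% | 1.74-1.77 | 1.080 / 1.025 / 0.975 |
| 50% | 2.20-2.26 | 1.122 / 1.069 / 1.020 |

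With 60% depressed, everyone at 10 or more sessions, and *e* = 15%, 25% or 33%, the odds ratios are 1.42, 1.61 and 1.75. At 50% depressed, the range for *e* = 15-33% is 1.45-1.81. Across the variants tried, the whole-arm values stay between roughly 0.9 and 1.15.

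**Sensitivity.** If 10% of non-depressed women are also extended (60% depressed, no low attenders, *e* = 15-33%), the odds ratio falls to about 1.1-1.35.

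**The case against.** The plan says only that the relationship will be assessed. It does not say that depression is regressed on sessions, and the model may stand in a fuller plan that is not shown. That is right, and the missing model is no fault. What remains is the stated purpose: no choice of model, trend test or table turns this plain association into an effective dose.

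A reader might infer that the analysis will show reverse causation, with more sessions looking harmful. The documents do not support that certainty. Only a minority is extended, and dropout linked to poor prognosis pushes the other way. Over the whole arm the illustrations fall on both sides of 1. The clear upward bias belongs to women with at least 10 sessions, under the assumed extension pattern.

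A reader might also take depression of 100% above 12 sessions as a finding. It is an input of the illustration. Being in crisis, or progressing but symptomatic, is not the same as meeting SCID-I criteria.

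Nor do the documents carry the result into the budget. The Budgetary impact analysis section varies programme size, the share of depressed mothers identified and nursing time. It does not use a dose-response estimate.

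Finally, this is one closing sentence on a non-primary analysis. The randomised primary comparison, its significance level and the sample size are untouched. That limits the weight of the point but does not remove it.

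**Conclusion.** Wrong as written. The plan sets a causal aim for a quantity that its own treatment rules make partly a result of the outcome and, for the 12-week outcomes, partly later than it. This follows from the text and needs no simulation.

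The size rests on assumptions. With no true dose effect, the odds ratio per session is about 1.3-1.8 among women with at least 10 sessions, when 10-33% of still-depressed completers and no recovered women are extended. It is about 0.9-1.15 over the whole arm when 20% have 0-9 sessions. The direction in the whole arm is therefore undetermined, and an observed gradient, or its absence, says little about dose.

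**What to change.** In the Primary analysis section:

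1. Drop the aim of determining an effective dose, and label the session-count analysis exploratory and non-causal.
2. For each outcome, count only sessions held before that assessment.
3. Report sessions 1-12 separately from extension sessions.

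Optionally, add a complier average causal effect with randomisation as the instrument. The Consent section supports this, since no formal telephone IPT programme exists in the participating regions, "thereby ensuring no mother in the control group will receive the intervention". Receipt of any session should be the main definition. The plan's 10-session threshold would assume that 1-9 sessions do nothing, and would overstate the effect if they help. With the planning figures, and reading the 80% as receipt of any session, a 20-point difference corresponds to 20/0.80 = 25 points among recipients. This answers a different question from dose-response, so it supplements the description and does not replace it.

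The cost is rewording, slightly more analysis work and the loss of an effective-dose claim. The IPT Activity Log already records sessions; session dates are needed, and the article does not say whether the log holds them. The complier analysis would bring a wide interval and an exclusion restriction that must be stated. Recruitment was still open, at 212 of 240, when the article was written, so the change could precede the analysis.
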